#### Demographics

At the first evaluation, characterization data will be recorded: gender, age, time post stroke, type of stroke (ischemic or hemorrhagic), affected side, and dominance.

#### Walking performance measures

To evaluate gait performance, we have chosen:

*6-min walk test (6min WT)* [30, 31]: This is used to characterize and monitor the gait changes in patients post stroke. It is commonly used to measure gait endurance and is a significant predictor for gait [32]. A systematic review published in 2017 showed that the clinically important difference (CID) for chronic hemiparesis patients varies from 28 to 42 meters [33].

*Timed up and go (TUG):* This is a simple test for functional mobility that requires the patient to move from sitting to standing, walking 3 m (as fast as possible), turning around (180°), walking back, and sitting again. The latency between letting go of backrest of the chair and then touching the backrest of the chair again after completing the walking is recorded. The best time of three attempts is to be used for the analysis. This is a common test used to evaluate the risk of falling and to monitor changes in patients’ mobility [34]. There is no defined value of CID for stroke patients; however, Hiengkaew et al. [35] shows that a change of ≥28% can indicate a relevant difference.

*10-m walk test (10mWT)*: This is a simple tool to quantify average speed during self-selected gait speed. The patient needs to walk in a hall with a 10-m demarcation, starting 1.5 m before the first mark and stopping 1.5 m after the last mark to exclude acceleration and slowdown. The stopwatch is started when the patient touches or crosses the first line and stopped when they touch or cross the last line. The CID for self-selected speed for stroke patients varies between 0.18 and 0.36 m/s (CI 95%) [35, 36].

*3-D gait analysis (3-DGA)*: This is performed at the Gait Laboratory. Subjects are equipped with skin-mounted reflective markers, placed on specific anatomical landmarks, as described by Kabada et al. [37]. Marker trajectories will be captured by an opto-electronic system consisting of eight infrared cameras (Qualisys OQUS300 system) operating at 100 Hz. Patients are instructed to walk barefoot at a self-selected speed along an 8-m walkway (26 feet). A minimum of six gait cycles for both lower limbs are collected, and a mean of these trials is obtained for the analysis and for consistency evaluation.

Kinematics are calculated according to a standard software procedure (Plugin Gait; Oxford Metrics, Oxford, UK) based on Kadaba et al. and Davis et al. [37, 38]. In order to improve the estimation of the thigh segment orientation, the Knee Alignment Device (KAD) was used during data collection.

From the kinematic data, the Gait Deviation Index (GDI) [39], the Gait Variable Scores (GVS), and Gait Profile Score (GPS) are calculated. The GDI is a multivariate measure of overall gait pathology. A GDI score equal to 100 or above indicates absence of gait pathology. Every 10-point decrease in GDI corresponds to one standard deviation from the mean of typically developing (TD) controls used during its calculation. The GVS is the root mean squared difference between a given kinematic variable calculated for a subject, and the mean of the same variable for a group of TD subjects. From all nine kinematic variables for which the GVS is calculated, an overall measure of gait pathology can be calculated (GPS). With all nine GVSs and the overall GPS, a Movement Analysis Profile can be plotted [40].

In a literature review, we found only one reference of minimal detectable change (MDC) for GDI scores related to post stroke patients. They suggest a MDC of 9.4 and 7.4 points for paretic and non-paretic limbs respectively [41]. For spatiotemporal parameters, we found these values for MDC: gait speed 14.61cm/s; stride length 11.96cm; cadence 8.58 step/min; step length 6.33cm; stance phase (StP) 3.60%; swing phase (SwP) 3.60%; and step width 2.47cm. For biomechanical parameters: hip maximum angle—SwP and StP 9.01° and 7.28°; hip minimum angle—SwP and StP 7.56° and 6.48°; knee maximum angle SwP and StP 6.54° and 4.93°; knee minimum angle SwP and StP 5.90° and 5.47°; ankle maximum angle SwP and StP 5.47° and 4.99°; ankle minimum angle SwP and StP 5.69° and 5.86° [42].

#### Balance measure

*Mini-Balance Evaluation Systems Test (Mini-BESTest)*: This is a tool used to evaluate balance control. It comprises 14 items divided into 4 subscales (anticipatory postural control, reactive postural control, sensory orientation, and gait stability). Each item is classified in an ordinal scale of 3 points (0 = severe and 2 = normal) and the maximum score is 28 points [43–45]. Tsang et al. [46] concluded that the MDC for this tool for post stroke patients is 3 points.

#### Self-reported measure

*Lower Extremity/Activity Log:* This is a structured interview, conducted by the therapist that evaluates how effectively subjects use their affected leg outside of the clinic setting in 14 common daily life activities on a scale that scores from 0 to 10 and quantifies functional performance (0 does not do and 10 does it normally) and the confidence with which the patient performs these activities (0 does not have confidence so does not do the task and 10 feels completely secure about doing the task). Patients are asked to score the quality of movement of the more-affected lower limb while performing the selected task, in the same way they are asked to score the confidence during this activity. LE/MAL has 3 dimensions: assistance scale, the functional ability scale, and the confidence scale. The assistance scale consists of 3 sub-scales: A, B, and C. Subscales A and B can take one of two forms, depending on the task. The form of subscale A (passive device-assistance) relevant to a given task can be either the orthotic subscale (A1) or the equipment modification subscale (A2). The scale for subscale B (self-initiated device-assistance) relevant to a given task can be either the assistive device subscale (B1) or the environmental support subscale (B2). Subscale C (person assistance) is the same for every item [25, 47, 48].

Instruments that are capable of measuring real-world/spontaneous use of lower limb are quite scarce. LE-MAL was not validated for Portuguese-Brazil language (our group is working on it). That is the reason for not using LE-MAL as one of our primary outcomes.

#### Data analyses

The software Excel (Microsoft) will be used to tabulate the data and the software SPSS will be used to do the statistical analysis. A significance level of 5% will be adopted.

We will use the Kolmogorov-Smirnov test to analyze the normality of the data. For the characterization of the sample and baseline comparison to test the homogeneity of the sample, the Qui-Quadrado will be used, but if we find statistical differences between the groups we will also analyze the clinical relevance of these differences.

The results will be compared in relation to the type of intervention and at the three timepoints proposed in this study (pre-treatment, post-treatment, and at 6 month follow-up) using the two-way analyses of variance, ANOVA, and the Bonferroni post-hoc test or Friedman, depending on the parameterization of the data.

To analyze the direction and magnitude of outcomes, we will use the Pearson or Spearman test of correlation.

The results will be described with mean and standard deviation for each group and mean and standard deviation of differences between groups and confidence interval.

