### Sample size and justification

After a sample size calculation, realized through a pilot study with 10 randomized patients in each group, using G*Power3.1.9.2 Software, we employed a matched-pair t-test *a priori*, using mean and standard deviation of Mini-BESTest (with an effect size of 0.93—sample size of 12 for each group) and 6minWT (with an effect size of 0.65—sample size of 21 for each group) as the primary outcome. Considering for analysis an α 0.05 and β 0.80, 21 patients were estimated for each group, totalizing 42 patients for this study.

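### The analysis of both primary outcomes is left to a data-dependent choice between two-way ANOVA and Friedman, and the Friedman branch does not compare the two arms

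*Protocol article*

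**What the plan says.** The protocol article, Data analyses, names one distributional check: "We will use the Kolmogorov-Smirnov test to analyze the normality of the data". Later in the same section, outcomes are to be compared by type of intervention and across the three time points, using two-way "ANOVA, and the Bonferroni post-hoc test or Friedman, depending on the parameterization of the data". The level is given once: "A significance level of 5% will be adopted".

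The Measurements section names two primary outcomes, Mini-BESTest and 6minWT. The Balance measure section describes the first: "Each item is classified in an ordinal scale of 3 points (0 = severe and 2 = normal) and the maximum score is 28 points". With 14 items scored 0 to 2, the total is an integer from 0 to 28. The Sample size section fixes the arm size: "Considering for analysis an α 0.05 and β 0.80, 21 patients were estimated for each group".

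The research question at the end of the Background section is whether LE-CIT is more effective than intensive conventional therapy, which is a comparison between arms.

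The article does not say which version of the Kolmogorov-Smirnov test is meant, whether raw scores, changes or residuals are tested, whether arms and visits are tested separately or pooled, or what happens when they disagree.

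**The concern.** A confirmatory analysis should be known before the data are seen. Here the article states a conditional choice between two methods for the primary outcomes. This is a rule that has been written down and is loose; it is not a detail merely left to another document.

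Two things could go wrong. First, the criterion may be a bad guide. A normality test on about 21 values has limited power against moderate skewness, and the Kolmogorov-Smirnov test assumes a continuous variable, so ties in an integer score inflate its rejections. Second, the two branches do not answer the same question. Two-way ANOVA contains group, time and their interaction. Friedman is a rank test for repeated measures in one sample and has no group factor. If a primary outcome goes down that branch, the comparison the trial was set up to make is no longer tested.

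**Working it through.** **The plan's own figure.** The article gives no operating figure for the normality step, so the figure to reproduce is the arm size, which sets the number of values per cell. The section says "we employed a matched-pair t-test". Power is P(|T| > t(0.975, n−1)), with T noncentral t and noncentrality d√n. Reading the stated β of 0.80 as power and taking two-sided 5%:
- d = 0.65 gives n = 21 (power 0.809).
- d = 0.93 gives n = 12 (power 0.834).

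Both stated sizes reproduce. Whether a paired formula suits two independent arms is a separate matter. Here it only fixes 21 per arm, 42 in all.

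**Inputs to the check.** From the article: 21 per arm, three visits, 5% level, integer score 0-28. Assumed, because the article gives no SD or distribution: Mini-BESTest normal with mean 14 or 15 and SD 5 or 4 (lower SDs as a range), rounded and held within 0-28; a skewed outcome as lognormal with CV 60%, that is log-scale SD √ln(1 + 0.6²) = 0.555; between-visit correlation 0.8; and a switch if any of the 2 × 3 = 6 arm-by-visit cells rejects.

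**The test.** D is the largest gap between the empirical distribution and a normal curve with the sample mean and SD. At n = 21 the 5% cut-off is 0.188 for the Lilliefors version, which allows for the estimated mean and SD, and 0.287 for the uncorrected version.

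**Firing rates, Lilliefors version**

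| Outcome | Per cell | Any of 6 cells |
|---|---|---|
| Exactly normal | 5% | about 24% |
| Rounded, SD 5 to 4 | 8-11% | 40-48% |
| Lognormal, CV 60% | 41% | 92% |

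The 24% is close to the value for six independent tests, 1 − 0.95⁶ = 26.5%; repeated runs gave 23-26%. With less spread the integer effect grows: per cell 16% at SD 3 and 32% at SD 2. Mild skewness is not well separated from harmless rounding. A score with skewness 1 is flagged in 19% of cells (66% for any of six), against 16% (63%) for a rounded normal score with SD 3.

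**Uncorrected version.** For normal data, or rounded data with SD 5-4, any of six cells fires in 0.5% of trials or fewer. The lognormal outcome is flagged in about 2% of cells.

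**What the switch does to type I error if the fallback compares arms.** Take a t-test on the T0-to-T1 change, replaced by Mann-Whitney when any cell rejects. Type I error stays between 4.5% and 5.5% over the normal, rounded and lognormal cases. Reporting whichever of the two tests is significant gives 5.5-6.5%.

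**What the switch does when the fallback is Friedman.** Let both arms improve by 0.6 SD with no difference between them (assumed, normal data, 21 per arm).
- ANOVA group-by-time at correlation 0.5: rejects in 4.8% of trials.
- Friedman on all 42 patients: rejects in 93% at correlation 0.5 and in over 99% at correlation 0.8.
- Friedman within one arm at correlation 0.5: rejects in 65%.

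These Friedman rejections are correct findings about time. They say nothing about the arms.

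**The case against.** Several objections have force.

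- **The gate is inferred.** No sentence says that a Kolmogorov-Smirnov p-value selects the method, or that the choice is made outcome by outcome. This stands. Even so, no other criterion is given, and on any reading the method depends on the data.
- **A reader might infer that the trigger is close to arbitrary.** The figures do not support that. It would mean setting any-cell false alarms (24%, or 40-48%) beside per-cell detection (41%). On one basis the Lilliefors version does discriminate: 5%, 8-11% and 41% per cell, or 24%, 40-48% and 92% for any cell. It is noisy on integers and weak against mild skewness, but it is not a coin toss.
- **A reader might infer that the primary analysis is left to chance.** Under the uncorrected version ANOVA is practically certain for normal or rounded data. The check is then uninformative, but the analysis is not random.
- **The six-cell rule is assumed.** Per test, exactly normal data are rejected 5% of the time by design. The 24% exists only if one cell of six is enough.
- **A reader might infer a seriously inflated type I error from the pre-test itself.** With a between-arm fallback there is almost none.
- **Version, unit and use of residuals may be settled in a fuller plan.** That is fair, and their absence is not the point here. The conditional choice is what the article states.

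**Conclusion.** The point holds in a limited form. The article fixes no single analysis for either primary outcome and lets the data choose between two. The only criterion it offers, a Kolmogorov-Smirnov test, suits 21 per arm and an integer 0-28 score poorly. The unstated version alone moves the switch probability for a rounded score from 0.5% or less to 40-48%, given SD 5-4, correlation 0.8 and an any-of-six rule, all of which are assumptions.

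The size of the harm lies in the destination of the switch. Type I error stays near 5% (about 6% if the better of two tests is reported) while the fallback compares arms. Friedman does not compare them. With equal improvement of 0.6 SD in both arms it is significant in 93% to over 99% of trials, and such a result could be misread as an effect of LE-CIT.

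One limit applies to the claim that no gate is needed. The simple two-arm t-test held 4.5-5.1% on skewed or rounded data, but the planned group-by-time ANOVA was simulated for normal data only. That is a reason to add a sensitivity analysis, not a reason to keep the gate.

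**What to change.** Drop both the normality gate and the Friedman branch. Name in advance one between-arm linear-model analysis for each primary outcome, and use it whatever a normality test shows. Either the group-by-time term of a repeated-measures model or the follow-up score compared between arms with adjustment for baseline would serve. Inspect the residuals of that model, and report a permutation (re-randomisation) p-value or a bootstrap confidence interval for the same arm difference as the sensitivity analysis. If a within-arm description over time is wanted, label it descriptive.

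The cost is one sentence of analysis text and one extra run, with no added patients or visits. The change should be dated before any comparison of the arms is made.

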**Methods:**

The study adopts a randomized, controlled, single-blinded study design. Forty-two patients, who suffered a stroke, who were in the chronic phase of recovery (>6 months), with gait disability (no community gait), and who were able to walk at least 10 m with or without the advice or support of 1 person, will be randomly allocated to 2 groups: the LE-CIT group or the control group (intensive conventional therapy). People will be excluded if they have speech deficits that render them unable to understand and/or answer properly to evaluation scales and exercises selected for the protocol and/or if they have suffered any clinical event between the screening and the beginning of the protocol. Outcome will be assessed at baseline (T0), immediately after the intervention (T1), and after 6 months (T2). The outcome measures chosen for this trial are as follows: 6-min walk test (6minWT), 10-m walk test (10mWT), timed up and go (TUG), 3-D gait analysis (3DGA), Mini Balance Evaluation Systems Test (Mini-BESTest), and as a secondary measure, Lower Extremity Motor Activity Log will be evaluated (LE-MAL). The participants in both groups will receive 15 consecutive days of daily exercise. The participants in the LE-CIT group will be submitted to this protocol 2.5 h/day for 15 consecutive days. It will include (1) intensive supervised training, (2) use of shaping as strategy for motor training, and (3) application of a transfer package (plus 30 min). The control group will receive conventional physiotherapy for 2.5 h/day over 15 consecutive days (the same period as the CIT intervention). Repeated measures analyses will be made to compare differences and define clinically relevant changes between groups.

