### Measurements

Patient from both groups will be evaluated at 3 time points: T0 - 1° pre-treatment (1–3 days before the beginning of the protocol), T1 - 2° immediately after the end of the protocol (1–3 days after the last day), and T2 - 3° 6 months after the end of the protocol. All the evaluations will be conducted by an independent, blinded, experienced and trained evaluator (Table 1).

**Table 1 Tab1:** Overview of measurements used in this study

Data	Time

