**Walking performance measures**	
6min WT	T0, T1, T2
TUG	T0, T1, T2
10mWT	T0, T1, T2
**3-D**	T0, T1

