**Balance measure**	
Mini-BESTest	T0, T1, T2

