**Self-reported measure**	
LE-MAL	T0, T1, T2

As primary outcomes we have chosen Mini-BESTest and 6min WT, one test for gait performance and one test for balance evaluation.

For the follow-up evaluations, patients will receive, at the end of the protocol, a date to return. Between 30 and 15 days before the date scheduled, we will call them to remember about that. In case of giving up from the protocol we will use all the data collected until the moment of renunciation (it has been predicted at the consent form).

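### The planned two-way ANOVA treats the T0 score as a third outcome level instead of adjusting for it, so the between-arm comparison of Mini-BESTest and 6minWT loses precision

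*Protocol article*

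**What the plan says.** The Measurements section takes every primary outcome before treatment in both arms: "Patient from both groups will be evaluated at 3 time points: T0 - 1° pre-treatment". Its Table 1 lists "Mini-BESTest T0, T1, T2" and "6min WT T0, T1, T2", and the text below it says "As primary outcomes we have chosen Mini-BESTest and 6min WT".

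Under Data analyses, the two arms are to be compared "at the three timepoints proposed in this study (pre-treatment, post-treatment, and at 6 month follow-up". The same sentence then names the method for that comparison: "using the two-way analyses of variance, ANOVA, and the Bonferroni post-hoc test or Friedman, depending on the parameterization of the data". The abstract describes the same plan: "Repeated measures analyses will be made to compare differences and define clinically relevant changes between groups". Results are to be reported with "mean and standard deviation of differences between groups and confidence interval".

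The only other use of T0 group differences is a baseline homogeneity test, with a judgement of clinical relevance if the test is significant. The T0 score is nowhere a covariate, and no reason is given for leaving it out.

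**The concern.** The research question is whether LE-CIT does better than intensive conventional therapy. In a group-by-time ANOVA with T0 as a response level, the answer can come from three places, and the plan does not say which:

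- **Group-by-time interaction.** Its T1-versus-T0 contrast is a comparison of change scores.
- **Bonferroni comparison of arm means at T1 or T2.** This ignores T0.
- **Group main effect.** This averages in T0, where randomisation makes the true difference zero.

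None of them conditions on the baseline. A change score over-corrects a chance imbalance, because it assumes a slope of 1 on T0; with equal SDs the slope is rho. A raw follow-up comparison does not correct at all. With 21 per arm the standard error of a baseline difference is √(2/21) = 0.31 SD, so a difference above 0.3 SD in either direction has a probability of about 33%. What is at stake is the width of the confidence interval for the treatment effect in a small trial.

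**Working it through.** **Inputs from the protocol.** Sample size and justification: 21 per group, effect size 0.65 (6minWT) and 0.93 (Mini-BESTest), alpha 0.05, and a stated beta of 0.80, read here as power. Data analyses: 5% significance level.

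**Assumptions.** Two-sided test; equal SD at every visit; rho is the correlation of T0 with follow-up, shown as a range because the protocol gives none; the effect sizes are taken as between-arm standardised differences.

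**The plan's own figures.** A two-sided paired t-test at 80% power gives n = 12 for 0.93 and n = 21 for 0.65, exactly as stated. The arms are independent, however. An independent two-sample test at 0.65 needs 39 per arm, and 21 per arm gives 54% power. That is a separate matter, but it sets the starting point here.

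**Variance of the between-arm comparison at one visit, relative to the raw score**

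- Raw T1 or T2: 1
- Change from T0: 2(1 − rho)
- Adjusted for T0 (ANCOVA): 1 − rho²

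So ANCOVA/raw = 1 − rho², and ANCOVA/change = (1 − rho²)/[2(1 − rho)] = (1 + rho)/2. At rho 0.5 both equal 0.75.

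**Power.** Noncentral t with noncentrality d√(21/2)/√v, where v is the relative variance; df 40, or 39 for ANCOVA.

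For 6minWT at rho 0.5:

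- Raw or change: 0.65 × 3.240 = 2.106, power 0.538.
- ANCOVA: 2.106/√0.75 = 2.432, power 0.660.

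For Mini-BESTest (0.93) at rho 0.5, power goes from 0.837 to 0.924.

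6minWT over the range, with 0.65 in follow-up-score SDs:

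| rho | Raw T1 | Change | ANCOVA |
|---|---|---|---|
| 0.3 | 54% | 41% | 58% |
| 0.5 | 54% | 54% | 66% |
| 0.6 | 54% | 63% | 73% |
| 0.7 | 54% | 76% | 82% |
| 0.8 | 54% | 90% | 93% |

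If 0.65 is instead in change-score SDs, the change comparison stays at 53.8%. ANCOVA gives 72.2, 66.0, 63.2, 60.6, 58.1 and 55.9% at rho 0.3, 0.5, 0.6, 0.7, 0.8 and 0.9. The gains are about 18, 12, 9, 7, 4 and 2 points.

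**The other two ANOVA terms** (compound symmetry, effects 0, d, d at T0, T1, T2, d = 0.65, rho 0.5)

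- 2-df interaction: noncentrality (21/2)[(2d/3)² + 2(d/3)²]/(1 − rho) = 10.5 × 0.2817/0.5 = 5.92 on 2 and 80 df, power 56%.
- Group main effect: mean difference 2d/3 = 0.433, SD √[(1 + 2rho)/3] = 0.816, standardised 0.531, power 39%.

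Both terms use two follow-up visits. The like-for-like comparator is the T1–T2 average adjusted for T0, with variance (1 + rho)/2 − rho² = 0.5 and power 83%. At rho 0.8 the interaction gives 93% and the adjusted average 98%.

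**Small-sample caveat.** The ANCOVA figures allow for the lost degree of freedom but not for estimating the slope. On average that inflates the variance by 1/(2 × 21 − 4) = 1/38, or 2.6%. This is trivial at rho 0.5 (0.75 becomes 0.77). It takes up about half of the 5% saving over the change score at rho 0.9.

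**The case against.** The strongest reply is that T0 is not ignored. In a group-by-time design the natural treatment term is the interaction, which uses T0 through change from baseline and is unbiased under randomisation. The abstract's wording on comparing differences fits that reading. The patients are chronic, and T1 follows T0 by about three weeks, so rho at T1 may well be high. At rho 0.7, 0.8 and 0.9 the confidence interval would narrow against the change score by only 1 − √0.85, 1 − √0.90 and 1 − √0.95, that is about 8%, 5% and 2.5%. The effect sizes also come from a paired calculation, so their use as between-arm differences is an assumption.

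Much of this stands as a limit on size. The plan is valid, the gain over a change-score contrast is modest at high rho, and the absolute power figures depend on the between-arm reading of 0.65 and 0.93. The variance ratios do not depend on those effect sizes. The plan also does not commit to the interaction: it names Bonferroni post-hoc comparisons without restricting them, and a raw T1 or T2 comparison loses more as rho rises. At T2, six months on, rho may be lower and the gain over change larger. A significance test of baseline homogeneity is not adjustment.

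**Conclusion.** The concern holds. The article fixes a model with T0 as a response level and no baseline covariate, so this is a stated method and not a detail left to an analysis plan. With equal SDs, conditioning on T0 gives a variance below the raw comparison for any nonzero rho and below the change comparison for any rho under 1, apart from the small cost of estimating one slope.

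The direction is firm; the size depends on a correlation that the protocol does not give. At rho 0.5 the saving is 25% of variance and 12 points of power for 6minWT. Against the change score it falls below 5 points from about rho 0.8. Against raw T1 means it grows to 39 points (54% to 93%) at rho 0.8. The planned analysis is inefficient, not biased, and should be changed because the improvement is nearly free.

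**What to change.** In Data analyses, replace the primary between-arm test with an ANCOVA or linear mixed model for each primary outcome:

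- **Responses:** T1 and T2 only.
- **Fixed effects:** treatment, visit, treatment-by-visit, the T0 value and T0-by-visit, with patient as the repeated subject.
- **Report:** the T0-adjusted LE-CIT minus control difference with its 95% CI at T1 and at T2, in metres and in Mini-BESTest points.
- **Other outcomes:** the same for 10mWT, TUG and LE-MAL, and for the T1 value of 3-D gait analysis, which has no T2 measurement.
- **Description:** keep unadjusted means and SDs.

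The Friedman alternative is a within-patient test that neither compares arms nor adjusts for T0. If a fallback for non-normal data is wanted, name one that does both, such as an ANCOVA on ranks, and judge normality on model residuals.

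The cost is a few sentences, one degree of freedom per covariate term and a simple rule for a missing T0 value. SPSS, already named, fits the model. No extra patients, visits or data are needed. Because data collection was under way at publication, the change should be a dated amendment made before outcome data are seen by arm.

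### The analysis section does not say that time is a within-patient factor or which effect tests the treatment, and it keeps T0 as an outcome level; a T0-adjusted mixed model would be clearer and, for a T1–T2 average, more powerful.

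*Protocol article*

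**What the plan says.** The Data analyses section sets out the comparison in one sentence. It opens "The results will be compared in relation to the type of intervention and at the three timepoints proposed in this study", lists pre-treatment, post-treatment and 6-month follow-up, and then gives the method: "using the two-way analyses of variance, ANOVA, and the Bonferroni post-hoc test or Friedman", with the choice between them left to the form of the data. The same section adds "A significance level of 5% will be adopted".

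The Methods paragraph of the Abstract describes the analysis differently: "Repeated measures analyses will be made to compare differences and define clinically relevant changes between groups".

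The Measurements section makes clear that the same people supply all three values: "Patient from both groups will be evaluated at 3 time points". It names the Mini-BESTest and the 6-minute walk test as primary outcomes, both recorded at T0, T1 and T2. It also says that data collected before a patient gives up will be used.

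The sample size section reports effect sizes of 0.93 (Mini-BESTest, 12 per group) and 0.65 (6-minute walk test, 21 per group), and says "we employed a matched-pair t-test *a priori*, using mean and standard deviation of Mini-BESTest". It concludes: "Considering for analysis an α 0.05 and β 0.80, 21 patients were estimated for each group, totalizing 42 patients for this study".

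**The concern.** The sentence in Data analyses leaves three things open.

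- **The within-patient factor.** Intervention and time point are the two factors, but nothing says that time is repeated within patients. An analyst working from this section alone could enter 42 × 3 = 126 values in an ordinary factorial ANOVA.
- **The treatment test.** A group-by-time ANOVA produces a group test, a time test and an interaction test. The section does not say which one answers whether LE-CIT is better than intensive conventional therapy. The group main effect averages in T0, when no treatment has been given. An unnamed test can also be chosen after the results are seen.
- **The fallback.** Friedman's test compares time points within patients and has no between-group factor. The Mini-BESTest is a sum of 14 three-level ordinal items, so the non-parametric branch could well be used for a primary outcome. On that branch the named test makes no comparison of LE-CIT with control.

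Both primary outcomes depend on this sentence.

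**Working it through.** **Plan's own figure.** For a two-sided paired t-test at α = 0.05, take the noncentral t with n − 1 df and noncentrality d√n.
- d = 0.65, n = 21: 0.65 × √21 = 2.98, power 0.809.
- d = 0.93, n = 12: 0.93 × √12 = 3.22, power 0.834.

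These are the smallest n that reach 0.80, so 21 and 12 reproduce, as numbers of pairs, with the stated β of 0.80 read as power.

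**Inputs for the comparison.** From the documents: 21 per group, three visits, 5% level. Assumed: two-sided tests, normal data, no dropout, and equal correlation ρ between any two visits, from 0.3 to 0.9 (the protocol gives none). Also assumed: the 0.65 is a between-group difference in SDs of change, present equally at T1 and T2. The protocol derives 0.65 from a matched-pair calculation, so this use of it is an assumption. With visit SD 1, the difference is δ = 0.65 × √(2(1 − ρ)).

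**A. Literal reading, visits independent, no true effect.**
- Group test: the variance of a patient's three-visit mean is (1 + 2ρ)/3, but the model assumes 1/3. Type I error ≈ 2[1 − Φ(1.96/√(1 + 2ρ))]. At ρ = 0.7 this is 2[1 − Φ(1.96/1.549)] = 20.6%.
- Interaction test: the within-patient variance is 1 − ρ, but the model assumes 1. Type I error ≈ 0.05^(1/(1 − ρ)). At ρ = 0.5 this is 0.05² = 0.25%.

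**B. Mixed reading, time repeated.** In simulation, every test keeps a type I error of 4.9% to 5.3%. Power:
- Group main effect: d = (2/3)δ/√((1 + 2ρ)/3), 40 df, noncentrality d√(21/2). At ρ = 0.7, δ = 0.503, d = 0.375, noncentrality 1.22, power 22%.
- Interaction (2 and 80 df): noncentrality 21δ²/(3(1 − ρ)) = 21 × 0.65² × 2/3 = 5.915, whatever ρ is. Power 56%.

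**C. T0 as covariate, 39 df, noncentrality d√(21/2).**
- T1 contrast: d = δ/√(1 − ρ²) = 0.65 × √(2/(1 + ρ)).
- T1–T2 average: residual variance (1 − ρ)(1 + 2ρ)/2, so d = 1.3/√(1 + 2ρ).

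| ρ | A: group type I error | A: interaction type I error | B: group main effect power | B: interaction power | C: T1 power | C: T1–T2 average power |
|---|---|---|---|---|---|---|
| 0.3 | 12.1% | 1.5% | 60% | 56% | 72% | 90% |
| 0.5 | 16.6% | 0.3% | 39% | 56% | 66% | 83% |
| 0.7 | 20.7% | 0.01% | 22% | 56% | 61% | 76% |
| 0.8 | 22.4% | about 0% | 15% | 56% | 58% | 72% |
| 0.9 | 24.3% | about 0% | 10% | 56% | 56% | 69% |

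The A columns are simulated (40,000 trials per setting) and agree with the formulas. The B and C columns are closed-form. Simulation gives 16% for the group main effect at ρ = 0.8, 55% to 71% for the T1 contrast and 68% to 89% for the average. The C figures run about one point lower there because the T0 slope has to be estimated.

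**The case against.** A reader might infer that the plan treats 126 visits as independent, that its tests are therefore invalid, and that the Abstract and the analysis section cannot both be followed. The documents do not support this. Nowhere do they say that visits are independent or that the patient is left out of the model. A group-by-time ANOVA with time repeated satisfies both texts, since one names the factors and the other the design. Two-way ANOVA is common shorthand for that model. The named fallback, Friedman, is itself a within-subject test. On this reading the type I error is 5%, and the figures under A do not arise. The descriptive means and SDs are unaffected on either reading.

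A reader might also infer that the diluted group main effect is the primary test. The section does not select it, and a factorial ANOVA ordinarily includes the interaction. Dilution is also not uniform: at ρ = 0.3 the group main effect, at 60%, is no weaker than the interaction.

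Finally, the primary contrast and covariance structure are often left to an analysis plan, which is not shown here. This objection stands as far as it goes, and it keeps the point from being an error in the plan. It does not remove the case for change. The article does name a method, that method keeps T0 as an outcome level, and its fallback makes no between-group comparison.

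**Conclusion.** Should-fix, as an improvement and not as a proven error. The section most likely means a mixed group-by-time ANOVA, but it does not state the repeated factor or the treatment test.

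On that reading, and under the assumptions listed, the interaction has about 56% power at any correlation. The group main effect has about 22%, 16% and 10% at correlations of 0.7, 0.8 and 0.9. A T0-adjusted contrast at T1 has about 55% to 71%, which is little or no gain over the interaction at high correlation. The T1–T2 average has about 68% to 89%, a clear gain throughout, but it depends on the effect lasting undiminished to six months.

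The type I error of 12% to 24% for the group test, with an interaction test that almost never rejects under the null, applies only if visits were analysed as independent. The documents do not say they will be. All power figures rest on reading 0.65 as a between-group effect, on the assumed correlations and on complete data.

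**What to change.** In Data analyses, replace the two-way ANOVA or Friedman sentence with text such as: Each primary outcome is analysed with a linear mixed model (SPSS MIXED) on the T1 and T2 values, with the T0 value as covariate, fixed effects for group, visit and group-by-visit, and correlated visits within patient. The treatment test is the T0-adjusted group difference at [T1, T2, or averaged over T1 and T2], fixed before results are seen.

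The sponsor should choose the contrast. T1 asks about the immediate effect, T2 about retention, and the average about both, with the most power if the effect persists. If a non-parametric fallback is kept, it should be one that compares the groups. The Abstract can stay as it is, because this model is a repeated-measures analysis.

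Patients who withdraw after T1 still contribute their T1 value, in line with the Measurements section; a classical repeated-measures ANOVA would drop them. Patients lost before T1 add no outcome value under this model.

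The cost is a few sentences, with the same data and software. The real decision is to commit to one contrast.
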